## Abstract

**Introduction::**

Nearly 20% of night shift nurses will cause shift work disorder (SWD) due to the disruption of sleep-wake cycle, which not only affects the daily work efficiency, but also brings a huge burden on physical and mental health. Acupuncture is a safe and effective intervention on SWD. This trial will combine with functional magnetic resonance imaging (fMRI) to study the clinical effects and potential mechanism of acupuncture in the treatment of SWD.

**Methods and analysis::**

This is a randomized controlled neuroimaging trial, with enrolled participants, outcome assessors, and data statisticians blinded. 60 patients with SWD and 30 healthy controls who sleep regularly will be recruited and divided into divided into a control group, a true acupoints treatment group (TATG) and a sham acupoints treatment group (SATG) by the ratio of 1:1:1. The TATG and SATG will receive 8 sessions of acupuncture treatment in 4 weeks. Cognitive function scales and MRI scanning will be performed before and after 4-week acupuncture treatment. The control group will receive no intervention. Functional connectivity of intra-network and inter-network will be the primary outcome and effect indicator. The secondary outcomes included Repeatable Battery for the Assessment of Neuropsychological Status, Attentional Network Test, Pittsburgh Sleep Quality Index scale and needle sensation assessment scale. Neuroimage indicators will be correlated with clinical data and scores of cognitive function assessment to explore the possible mechanisms underlying the changes of brain activity caused by acupuncture treatment.

**Discussion::**

The results of this study will enable us to verify the therapeutic effect of acupuncture on SWD and explore the potential central mechanism of acupuncture on SWD from the change of brain activity.

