### Sample size

2.6

When calculating the sample size during the acupuncture-neuroimaging study, the number in published literature and previous studies is often considered. On the one hand, in fMRI studies, millions of voxels are used to estimate the blood oxygen level dependent (BOLD) signal indirectly, and conventional power calculations often make no sense. On the other hand, the number of participants is often constrained by scanning time and costs. In hence, considering the published acupuncture-neuroimaging literature focusing on sleep disorder, the sample size range of 16 to 32 cases show enough statistical power for brain functional analysis.^[21]^ In the present study, we plan to recruit 60 patients with SWD and 30 healthy subjects with regular sleep.

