### Randomization and blinding

2.7

Randomization will be carried out in 2 steps. Firstly, according to the inclusion exclusion criteria, the 90 participants will be divided into experimental group and control group by the ratio of 2:1; secondly, the patient with SWD will be divided into TATG and SATG according to the computer-generated random sequence using Excel's rand function (1:1 ratio). The code will be sealed in opaque envelopes and opened by researchers not involved in the recruitment following informed consent procedures and baseline testing, with direct responsibility for treatment allocation. The researchers and acupuncturists will know the allocation. Meanwhile, the participants, outcome assessors and data analysts will be blinded.

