## Interventions

3

Patients with SWD will receive true or sham acupuncture treatments for 4 weeks, while healthy subjects will receive no intervention.

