### Sham acupuncture group

3.2

Patients in sham acupuncture group will receive 4-week manual acupuncture treatments at 10 sham acupoints (SA). According to the previous literature on setting locations of SA,^[22]^ the SA should be set aside with 1 inch beside the true point as the sham acupoint. In hence, the deqi experience of the participants in SATG will not be overemphasized. In spite of the locations of acupoints, the treatment procedures and course will be the same with TATG.

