## Discussion

6

Acupuncture is a common therapy for insomnia in China, and great progress has been made in the study of its pathogenesis.^[29]^ Systematic reviews and a large number of trials have confirmed that acupuncture is safe and effective in the treatment of insomnia.^[30,31]^ However, there are few studies on acupuncture treatment of SWD. Previous studies and literatures have shown that acupuncture can effectively treat insomnia and sleepiness of shift work disorder, and improve attention decline.^[32]^ In the current research, we will focus on the effect of acupuncture on cognitive functions of patients with SWD, and explore the neural mechanism of acupuncture on SWD through fMRI.

A large number of studies showed that, the activity of cerebral cortex and the internal and external functional connectivity of neural network were closely related to the occurrence of shift work disorder.^[33,34]^ Meanwhile, the fMRI technology provides a direct tool for the study of brain response to acupuncture intervention. Numerous studies revealed changes of the brain's intrinsic functional connectivity stemming from cognitive impairments on patients with sleep disorder.^[23,24]^ A previous study also reported that patients with SWD showed brain perfusion changes in multiple brain areas significantly correlated with insomnia severity.^[35]^ In this study, the relationship between acupuncture sensation and fMRI is preliminarily discussed. fMRI can infer that regional changes in brain activity reflect whether specific brain regions or resting-state brain networks are involved in improvements of cognitive functions after 4-week acupuncture treatments.

However, there are few studies on acupuncture in the treatment of SWD, which need to be further studied through larger, more rigorous and good randomized clinical trials. At the same time, the purpose of setting up the false acupuncture group in this study is to eliminate the placebo effect. However, it is difficult for Chinese patients to choose the sham acupoint as the acupuncture placebo. As patients may have their own acupuncture treatment experience and know the location of common acupoints. In hence, the blinding of patients in this study has a certain impact.

In conclusion, the purpose of this study is to evaluate effect of acupuncture on cognitive impairments of SWD and to interpret the neural mechanism of acupuncture on SWD through fMRI.

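### The design tests true-point against sham-point needling within SWD; the claim to verify the therapeutic effect of acupuncture on SWD is broader than that

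*Protocol article*

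**What the plan says.** All references are to the protocol article.

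- **Claim.** The Discussion paragraph of the abstract says the results will "verify the therapeutic effect of acupuncture on SWD and explore the potential central mechanism of acupuncture on SWD". The end of section 1 expects them to support use of acupuncture for SWD in practice. Section 6 closes by giving the purpose as evaluating the effect of acupuncture on cognitive impairment in SWD.
- **Groups.** Section 2.6: "we plan to recruit 60 patients with SWD and 30 healthy subjects with regular sleep". Section 2.7 describes two steps. Eligibility separates SWD patients from healthy controls; a random sequence then splits the SWD patients 1:1 into TATG and SATG.
- **Untreated group.** Section 3 has all SWD patients needled, "while healthy subjects will receive no intervention". Section 2.4 selects the healthy group for regular sleep.
- **Sham.** Section 3.2 prescribes manual acupuncture at 10 sham points: "the SA should be set aside with 1 inch beside the true point as the sham acupoint". Apart from location, "the treatment procedures and course will be the same with TATG". It also says that "the deqi experience of the participants in SATG will not be overemphasized". In section 3.1, needles in TATG are inserted 0.5 to 1 inch deep and retained for 20 minutes once deqi has been obtained by manipulation.
- **Purpose of the sham.** Section 6: "the purpose of setting up the false acupuncture group in this study is to eliminate the placebo effect".
- **Analysis.** Section 5.1 compares clinical and cognitive scores across the three groups by one-way ANOVA, followed by two-group comparisons that are not named. Section 5.2.2 uses one-way ANOVA with FDR correction for functional connectivity, the primary outcome.

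**The concern.** A claim about the effect of acupuncture on SWD needs a contrast that contains that effect. Here every SWD patient is needled and everyone left unneedled is healthy, so no group shows what untreated SWD patients would do over 4 weeks on repeat RBANS, ANT, PSQI and scans. The sham is itself needle insertion, so the true-sham difference removes placebo and also anything needling does regardless of site. The stated purpose of the sham describes only the first of these.

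What is at stake is the conclusion the trial may draw. Under the abstract's wording, a true-sham null has no agreed reading. A three-group ANOVA can also give a significant result that reflects disease status rather than treatment.

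**Working it through.** No figure in the plan is disputed. The group sizes agree: 90/3 = 30 and 60/2 = 30. The question is which effects the group means can identify.

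**Step 1: what each mean change contains.** Assume additive components: *n* = change in untreated SWD (natural course, retest learning, regression to the mean); *P* = placebo effect, taken as equal in both needled arms; *G* = effect of needling that does not depend on site; *S* = added effect of the true points; *h* = change in healthy subjects.

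- TATG change = n + P + G + S
- SATG change = n + P + G
- Healthy change = h

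**Step 2: what each contrast gives.**

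| Contrast | Randomised? | Estimates |
|---|---|---|
| TATG − SATG | yes | S |
| TATG − healthy | no | (n − h) + P + G + S |
| SATG − healthy | no | (n − h) + P + G |
| Before-after within TATG | no comparator | n + P + G + S |

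Acupuncture against no acupuncture in SWD is P + G + S. Acupuncture beyond placebo is G + S. Three means identify S, h and the sum n + P + G. They do not split that sum, so neither quantity can be recovered, and a larger sample does not help.

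**Step 3: what a result would mean.**

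- *TATG better than SATG.* S > 0: randomised evidence of a point-specific benefit. Since TATG v untreated = (TATG − SATG) + (SATG − untreated), it is also a lower bound on the total effect if sham needling does no harm.
- *No difference.* S is near 0 or was missed. Nothing follows about P + G.

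**Step 4: the three-group ANOVA.** Suppose TATG and SATG have identical means and the healthy mean differs by δ. With 30 per group the grand mean is δ/3 above the SWD mean. The between-group sum of squares is 30 × [(δ/3)² + (δ/3)² + (2δ/3)²] = 30 × (6/9)δ² = 20δ². It is above zero whenever healthy subjects differ from SWD patients, with no treatment difference at all. Only the TATG v SATG pair carries treatment information, and neither section 5.1 nor section 5.2.2 names it.

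**Step 5: the deqi wording.** Section 3.1 makes deqi a condition for starting retention. Section 3.2 says the procedures are the same, yet plays down deqi in SATG. If both arms seek deqi, S is an effect of site. If SATG does not, S is an effect of site plus stimulation. The identification result in Step 2 stands either way, but the correct description of the contrast changes.

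**Illustration only.** These effect sizes are assumptions; none is in the document. Let the total effect be D and let sham keep a share s of it, so TATG − SATG = D(1 − s). For a two-sample t-test, 30 v 30, two-sided 0.05:

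| D (SD) | s | Contrast (SD) | Power |
|---|---|---|---|
| 0.5 | 0 | 0.50 | 48% |
| 0.5 | 0.5 | 0.25 | 16% |
| 0.8 | 0 | 0.80 | 86% |
| 0.8 | 0.5 | 0.40 | 33% |

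The table shows how a null could arise although acupuncture works. It does not bear on identification and does not represent the FDR-corrected connectivity outcome.

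**The case against.** A reader might infer that the trial cannot show any therapeutic effect. The document does not support that. TATG v SATG is a randomised, sham-controlled comparison within SWD, with RBANS, ANT and PSQI among its outcomes. Retest learning and regression to the mean are balanced by randomisation in that contrast, and a TATG advantage would be sound evidence for needling at the named points. This objection stands and sets the limit of the finding.

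A reader might also infer that the authors intend to read a null as no effect, or within-arm gain as efficacy. No section says so. The point is only that the broad claim and the unnamed comparisons leave these readings open.

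Nothing in the document shows that needling 1 inch away has a physiological effect, and the source cited for the sham location cannot be checked here. That also stands: G is unknown, and may be zero. But the design cannot show that it is zero, which is what the broad claim needs.

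A sham comparator without an untreated SWD arm is a legitimate design choice, and a separate analysis plan may name the efficacy contrast. The first is granted, and no new arm is asked for. The second would settle part of the analysis point but would not narrow the abstract's claim. Section 6 admits a weakness of sham points, but only for blinding; it mentions neither the subtraction of site-independent effects nor the missing untreated SWD arm.

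**Conclusion.** The point holds as one about scope. The trial can estimate a single randomised effect, true-point against sham-point needling in SWD. It cannot estimate acupuncture against no acupuncture in SWD, and the abstract claims more than the design delivers. The three-group ANOVA mixes disease status with treatment unless the TATG v SATG pair is singled out.

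The size of the problem lies in what may be concluded; no stated number is wrong. The result rests on the group structure and on sham being needle insertion, both stated in the document, and on additivity with equal placebo effects in the two needled arms, which is assumed. Section 6 itself doubts patient blinding; if placebo effects differed between the arms, the contrast would carry that difference too. To say that only the site differs would go too far while sections 3.1 and 3.2 disagree on deqi.

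**What to change.** 1. In the abstract's Discussion paragraph, the last paragraph of section 1, and section 6, restate the treatment question as needling at the named acupoints compared with the sham needling 1 inch beside them. Replace the statement that the sham eliminates the placebo effect with one saying that it removes placebo together with any effect of needling that does not depend on site.
2. In sections 5.1 and 5.2.2, name TATG v SATG, on change from baseline, as the sole efficacy contrast. Use the healthy group only as a reference for normal connectivity and cognition.
3. State that before-after change within either needled arm is not evidence of efficacy, and that no TATG-SATG difference will not be read as no effect of acupuncture.
4. List the absence of an untreated SWD arm as a limitation in section 6.
5. Reconcile sections 3.1 and 3.2 on whether deqi is sought in SATG, and describe the contrast accordingly.

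No arm, sample size or schedule changes. The work is rewording plus one named contrast. The price is a narrower claim.

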## Introduction

1

Shift work disorder (SWD) is a condition defined by excessive sleepiness or insomnia accompanied by total sleep time reduction.^[1]^ According to the epidemiology, SWD effects approximately 10% to 38% of the shift worker population. Nurses make up the largest proportion of shift workers (15%–20%).^[2]^ Evidence suggests that long-term shift work will not only affect work efficiency and patient satisfaction, but also lead to physical and mental health problems.^[3,4]^ In hence, given enough time, this may lead to more severe disorders, such as cardiovascular disease, cerebrovascular events, metabolic disorders, gastrointestinal complaints and multiple forms of cancer.^[5–7]^ Meanwhile, SWD also impairs cognition, such as attention and memory, which will directly affect work efficiency or even cause safety consequences not only for the individuals concerned, but also for society. Therefore, it is essential to explore an effective intervention on impairments of cognitive abilities for patients with SWD.

Medication is the main effective method to treat shift work sleep disorder,^[8]^ Such as benzodiazepines, nonbenzodiazepines and antihistamines. These drugs have a definite effect to a certain degree, while side effects may occur following a long time medication.^[9]^ The most common symptoms are headache, dizziness, nausea and anxiety.^[10]^ Clinical studies have confirmed that long -term taking benzodiazepines and non-benzodiazepines could impair attention, memory, response speed and mental activity,^[11,12]^ even increasing the risk of Alzheimer's disease.^[13]^ Furthermore, with the accumulation of drugs will lead to addiction.^[14]^ In hence, it is necessary to explore a safe and effective method to treat SWD.

Acupuncture, as one of the traditional treatment methods in China, has a long history in the treatment of sleep disorder.^[15]^ Abundant randomized controlled trials have confirmed that acupuncture treatment on insomnia has the advantages of stable effect and less side effects.^[16–19]^ A recent study also confirmed that manual acupuncture could improve memory function in chronic insomniacs. In hence, it is essential to definite efficacy of acupuncture treatment on cognitive decline. However, to our knowledge, there is no study focusing on acupuncture therapy on SWD.

In this study, we will conduct a randomized controlled trial to study the effect of acupuncture on cognitive abilities of SWD and reveal the underlying neuroimaging mechanism. The results will provide evidence and promote acupuncture therapy on SWD during clinical practice.

## Methods

2

### Study design

2.1

This is a randomized controlled, paralleled neuroimaging study, with patients, assessors and data statisticians blinded to the group assignment. A total of 60 patients with SWD and 30 healthy subjects will be recruited from October 2019 to December 2020 at Beijing Anding Hospital of Capital Medical University. They were divided into a control group, a true acupoints treatment group (TATG) and a sham acupoints treatment group (SATG) by the ratio of 1:1:1. The TATG and SATG will receive 8 sessions of acupuncture treatment in 4 weeks (2 sessions every week) by a trained acupuncture operator. Cognitive function scales and MRI scanning will be performed before and after 4-week acupuncture treatment. Meanwhile, the needle sensation will be evaluated by assessment scale after each session. The control group will receive no intervention.

The study procedures are detailed in Figure 1.

**Figure 1 F1:**
[figure not shown]
Flowchart of study design. ANT = Attentional Network Test, FC = functional connectivity, PSQI = Pittsburgh Sleep Quality Index scale, REBANS =  Repeatable Battery for the Assessment of Neuropsychological Status, SATG = sham acupoints treatment group, SWD = shift work disorder, TATG = true acupoints treatment group.

### Participants and recruitment strategy

2.2

A total of 90 participants will be recruited from October 2019 to December 2020 at Beijing Anding Hospital of Capital Medical University through posters and other publicity methods. Patients with SWD or healthy subjects who match the inclusion criteria will be considered potential participants. If they are eligible and interested in participating in the study, they will be fully informed of the entire study procedures, benefits and risks. Written informed consent will be obtained from the patient or their legally authorised representative before the allocation. Each participant has the right to withdraw from the study unconditionally.

### Inclusion criteria of TATG and SATG

2.3

Patients will be enrolled if they meet the following criteria: meeting the diagnostic criteria for SWD according to International Classification of Sleep Disorders (2nd Edition) by the American Sleep Disorders Association;^[20]^ female nurses working at Beijing Anding Hospital; aged from 18 to 40 years, right-handed; continuous regular night shift for at least 1 year and work for 5 to10 years, at least 2 shift work per week; with no history of prophylactic or therapeutic medicine in the past 3 months; with no history of long-term use of analgesics.

### Inclusion criteria of control group

2.4

Healthy subjects will be recruited following inclusion criteria: relative regularity of sleep in the past 12 months; aged 18 to 40 years, right-handed; sleeping less than 3 times per month after 23 o’clock in the latest 1 year and night shift less than 3 times a month in the latest 1 year.

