### Exclusion criteria

2.5

Participants will be ruled out if they meet any criteria below: pregnant or lactation; history of neurologic or psychiatric disorders; participating in such cognitive experiments within 1 year; any other health problems or poor physical conditions that may influence participation; any brain structure damage or abnormalites identified by MRI examinations; any history of alcohol or drug dependency; any MRI contraindications.

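### Patients are restricted by sex, occupation and medication but the non-randomised healthy controls are not, so the patient-versus-healthy contrast and the three-group test may mix SWD with those factors

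*Protocol article*

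**What the plan says.** **Patients (2.3).** Eligible patients are "female nurses working at Beijing Anding Hospital; aged from 18 to 40 years, right-handed". Their work history must show "continuous regular night shift for at least 1 year and work for 5 to10 years, at least 2 shift work per week". They must also be "with no history of prophylactic or therapeutic medicine in the past 3 months; with no history of long-term use of analgesics".

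**Healthy controls (2.4).** The criteria are "relative regularity of sleep in the past 12 months; aged 18 to 40 years, right-handed", few late nights, and "night shift less than 3 times a month in the latest 1 year". Sex, occupation, years in work, medicines and analgesics are not mentioned.

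**Exclusions for everyone (2.5).** These cover pregnancy or lactation, neurologic or psychiatric history, recent cognitive experiments, brain abnormality, alcohol or drug dependency and MRI contraindications. There is also a general clause: "any other health problems or poor physical conditions that may influence participation". None of them restricts sex, occupation or current medication.

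**Recruitment and allocation (2.2, 2.7).** Participants are recruited "through posters and other publicity methods". Controls form their group by eligibility; only the patients are randomised, 1:1, to true or sham acupoints.

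**Analysis (5.1, 5.2.2).** Cognitive scores and functional connectivity, the latter being the primary outcome, are each compared across the three groups by one-way ANOVA. No covariate is named. The baseline items in 4.1 include sex and age but not education, occupation or medication.

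**The concern.** The healthy group is not descriptive background. It enters the omnibus test of the primary outcome and of the cognitive scores. Because it is not randomised, its comparability with the patients depends on the eligibility criteria, on any matching and on the analysis. Here the two eligibility lists are both given, and they differ on characteristics that the plan itself thought worth fixing in patients.

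Resting-state connectivity, RBANS and ANT scores could plausibly differ by sex, education, occupation or medicine use. If the controls differ from the patients on these, a significant three-group result, or a patient-versus-healthy difference, could not be attributed to SWD alone. The nominal age range is the same in both lists, but a minimum of 5 years in work makes the youngest ages practically unreachable for patients while leaving them open to controls.

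This is more than a detail that a condensed article leaves to a fuller document. Eligibility is stated in full for both groups, and the stated rules allow the imbalance.

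**Working it through.** **Step 1: the two lists side by side.**

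| Characteristic | Patients (2.3) | Controls (2.4, 2.5) |
|---|---|---|
| Sex | Women only | No criterion |
| Occupation and site | Nurse at the study hospital | No criterion |
| Years in work | 5 to 10 | No criterion |
| Medicine, past 3 months | None | No criterion |
| Long-term analgesics | None | No criterion |
| Age | 18 to 40 | 18 to 40 |
| Handedness | Right | Right |
| Night shifts | At least 1 year of regular night shift; at least 2 shifts a week | Fewer than 3 a month |

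The last row is the intended contrast and is not a confounder. The first five rows are the gap.

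**Step 2: group sizes.** 90 x 2/3 = 60 patients and 90/3 = 30 controls; 60/2 = 30 per acupuncture group. The split is consistent. The article gives no power, effect size or SD, so there is no stated figure to reproduce.

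**Step 3: size of the possible bias, using sex as the example.** The inputs are assumptions, not document figures. A share m = 0.5 of controls are men (0 among patients), the sex effect d is 0.3 to 0.5 SD, and there is no true SWD or acupuncture effect.

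Bias b = m x d:
- 0.5 x 0.3 = 0.15 SD
- 0.5 x 0.5 = 0.25 SD

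**Step 4: effect on the planned test.** For three groups of 30 with means 0, 0 and b, the grand mean is b/3. The noncentrality is 30 x [2 x (b/3)² + (2b/3)²] = 30 x (6b²/9) = 20b². The 5% critical value of F on 2 and 87 degrees of freedom is 3.10.

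| b | Noncentrality 20b² | Rejection rate |
|---|---|---|
| 0.15 | 0.45 | 8.4% |
| 0.25 | 1.25 | 15.1% |

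These are rates per test against a nominal 5%, before FDR correction. FDR handles multiplicity; it does not remove a bias.

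**Step 5: sensitivity to the assumptions.** Same ANOVA over a wider range:

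| m | d = 0.2 | d = 0.5 | d = 0.8 |
|---|---|---|---|
| 0.25 | 5.4% | 7.3% | 11.3% |
| 0.5 | 6.5% | 15.1% | 33.0% |

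With m = 0 (women only) this source of bias is zero and the rate returns to 5%.

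**Step 6: can analysis repair it?** For sex, yes, under an additive model. A simulation of 60 patients against 30 controls, half of them men, with d = 0.5 SD and no SWD effect, gave a sex-adjusted bias near 0 and a rejection rate of about 4.5%. The price is precision. The standard error of the contrast rises from √(1/60 + 1/30) = 0.224 SD to √(1/60 + 1/15) = 0.289 SD, because the comparison then rests on the 15 female controls.

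**The case against.** The strongest reply has five parts.

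- **The criteria permit imbalance; they do not create it.** This stands. The night-shift limit for controls fits day-working hospital staff, and the posters may attract mostly women. A reader might infer that the comparison is confounded whatever happens; the text does not support that.
- **Healthy volunteers are unlikely to be on medicines.** This largely stands. Healthy status and the general health exclusion in 2.5 make substantial drug use unlikely, but do not bar it. Medication is the weakest of the three factors.
- **Sex is recorded, so it can be adjusted for.** This stands. It is tempting to say that adjustment must fail because there are no male patients. That is wrong: the sex effect can be estimated within the controls, and the adjusted contrast becomes patients against female controls (step 6). Occupation, education and medication are different, because 4.1 does not list them.
- **The acupuncture question is answered by the randomised groups.** This stands for true against sham acupoints. A reader might infer that the treatment effect is biased, or that the plan intends to claim that acupuncture restores healthy connectivity. The article makes no such claim, and the randomised contrast does not use the controls. If the ANOVA were run on change from baseline, a constant difference in level, such as one due to sex, would also cancel.
- **Matching and covariates may sit in a fuller document.** Their absence from an article is not itself an error. The point rests on the difference between the eligibility lists in 2.3 and 2.4.

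**Conclusion.** The point holds within limits. The stated eligibility rules allow the non-randomised controls to differ from the patients in sex, occupation and medication. The patient-versus-healthy contrast and the three-group omnibus tests in 5.1 and 5.2.2 may therefore mix SWD with those factors. The randomised comparison of true with sham acupoints is untouched.

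The asymmetry is certain from the text; its size is not. If half the controls are men and the sex effect is 0.3 to 0.5 SD, the bias is 0.15 to 0.25 SD and the planned ANOVA rejects about 8% to 15% of the time instead of 5%, per test and before FDR. With a quarter of controls male and an effect of 0.2 SD, the inflation is negligible (5.4%). A pooled t-test of 60 against 30 would give higher rates, about 10% to 20%, but the article does not plan that test, so those figures should not be used. The change is worth making because it is cheap at the design stage, while a later repair costs precision or needs data not listed for collection.

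**What to change.** 1. In 2.4, restrict controls to women and apply the same medication and analgesic criteria as in 2.3.
2. Where feasible, recruit controls from day-working nursing staff or comparably educated staff, and balance them with the patients on age. Strict matching on years in work may not be achievable at one hospital and need not be required.
3. Add education and occupation to the baseline items in 4.1.
4. State that the patient-versus-control contrast is adjusted for age and education.
5. If male controls are already enrolled, adjust that contrast for sex or analyse female controls only. Either removes the sex bias, at some cost in precision.

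Cost: an eligibility amendment affecting 30 untreated volunteers, two more baseline items and a smaller pool from which to recruit controls.
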